### Participant timeline {13}

Administration will occur as per the Time and Events Schedule in Table 5. Clinical visits will occur as needed and will be determined during the initial assessment. Clinical visits are not outlined in the time and event schedule as these are a part of routine care. Self-report measures will be completed at home prior to each study visit using the study Electronic Data Capture System (EDCS). Participants will be able to leave and return to the questionnaires whenever they need to complete them. It is anticipated the first and last visit will take approximately 45 min, while weeks 4 and 8 will take approximately 30 min. Participants will complete the WHODAS first and all responses are mandatory. All other self-report measures will be completed in a structured order.

**Table 5 Tab5:** Time and events schedule

Measures	Time to complete (minutes)	Administration	Baseline	Week 4	Week 8	Week 12
WHO Post COVID CRF Module 1	Variable	Chart review	**X**			
WHO Post COVID CRF Module 2	Variable	Chart review	**X**			**X**
WHO Post COVID CRF Module 3	Variable	Chart review	**X**			**X**
Demographics	<5	Self-report	**X**			
ACE-Q	5	Self-report	**X**			
Injustice Experience Questionnaire (IEQ-SF)	<5	Self-report	**X**			
WHODAS	5	Self-report	**X**	**X**	**X**	**X**
PHQ-9	<5	Self-report	**X**	**X**	**X**	**X**
GAD-7	<5	Self-report	**X**	**X**	**X**	**X**
PCL-5	5	Self-report	**X**	**X**	**X**	**X**
EQ-5D-5L	<5	Self-report	**X**	**X**	**X**	**X**
AUDIT	<5	Self-report	**X**			**X**
ASSIST	5-10	Interview	**X**			**X**
Fatigue Severity Scale	<5	Self-report	**X**	**X**	**X**	**X**
PSQI	5	Self-report	**X**	**X**	**X**	**X**
Warwick-Edinburgh Mental Wellbeing Scale (WEMWBS)	5	Self-report	**X**			**X**
Pain Numeric Rating Scale	<5	Self-report	**X**	**X**	**X**	**X**
MRC Dyspnoea Scale	<5	Self-report	**X**	**X**	**X**	**X**
Cognition (Trailmaking, Hopkins Verbal Learning, Digit Span, Phonemic/Semantic Verbal Fluency)	30	Interview	**X**			**X**
Qualitative Interview (Optional)	30	Interview				**X**

### Sample size {14}

We have based the sample size calculation on the sum of domain scores of the WHODAS 36, as the recommended assessment for Long COVID patients [33]. At the time of writing this protocol, there were no published scores of the WHODAS 36 in people with Long COVID. Therefore, we have based our sample size calculation on WHODAS 36 scores from 25 randomly selected patients attending an existing clinic for Long COVID at TOH run by OWN. These patients had a mean sum of domain scores of 17 (SD=4). The minimally important clinical difference on the WHODAS 36 is about a 10% change in scores [32]. Using these assumptions, we need to recruit at least 126 participants (63 in each group) to have 80% power to detect a 10% change in scores assuming an alpha of 0.05. Allowing for 20% drop out would mean a recruitment target of 152 (76 in each group) people.

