### Eligibility criteria {10}

Participants will be recruited from TOH. Participants will be approached by an individual in their circle of care if they meet the eligibility criteria outlined in Table 1.

**Table 1 Tab1:** Eligibility criteria

Inclusion criteria	
Participants must:	
1.	Be 18 years of age or older
2.	Have a confirmed diagnosis of COVID-19 with a PCR test at least 12 weeks prior OR a confirmed rapid antigen test at least 12 weeks prior OR meet Ottawa Public Health guidance for a suspected COVID-19 case (Table 2)
3.	Have at least one ongoing symptom consistent with Long COVID as measured by the WHO Post COVID Case Report Form (CRF)
4.	Have a minimum WHO Disability Assessment Scale (WHODAS) self-report (36 item) sum score of 15
5.	Be willing to use email for study activities
6.	Be able and willing to use an electronic platform, either on smartphone or computer web browser, for the duration of the trial
7.	Be able to read and understand English or French.
8.	Be willing and able to provide informed consent.
Exclusion criteria	
Participants must not:	
1.	Have any significant functional impairment (for example, advanced dementia, heart or lung disease) as judged by the assessing clinician
2.	Participate in another Long COVID trial where treatment is required in the protocol (pharmacological or behavioral). Observational studies will be allowed.
3.	Have symptoms consistent with Long COVID that are better explained by an alternative diagnosis

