### Criteria for discontinuing or modifying allocated interventions {11b}

Decisions about modifying individual rehabilitation care or health coaching will be made in collaboration with the most responsible healthcare provider and the Principal Investigator. No predefined criteria will be used with respect to modifying individual interventions.

The trial will be stopped if more than 25% of participants in the intervention group experience at least a 20% increase in severity in their WHODAS sum score. There will be no stopping criteria for benefit given the short duration of the study.

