### Outcomes {12}

#### Primary outcome

To evaluate the primary outcome, improvement in quality of life, we will use the total sum score of the WHO Disability Assessment Scale (WHODAS 2.0) self-assessment. The WHODAS is a 36-item self-report questionnaire measuring health and disability from the previous 30 days across six domains of functioning: cognition, mobility, self-care, getting along, life activities, and participation. Responses are scored on a 5-point Likert scale: None [0], Mild [1], Moderate [2], Severe [3], and Extreme/Cannot Do [4] [32].

The WHODAS 2.0 has been validated using a cross-cultural approach in 19 countries and within 4 subgroups (general population, populations with physical problems, populations with mental or emotional problems, and populations with problems related to substance use). The WHODAS 2.0 showed excellent overall test-retest reliability (ICC=0.98) and internal consistency (Cronbach’s alpha = 0.98). The survey also showed good cross-cultural sensitivity and concurrent validity [32].

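### The score behind the sample size (mean 17, SD 4) is undefined and labelled differently from the primary outcome, and its stated inputs do not give 80% power at 63 per group

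*Protocol article*

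**What the plan says.** Under Outcomes {12}, for the primary outcome, "we will use the total sum score of the WHO Disability Assessment Scale (WHODAS 2.0) self-assessment". The same paragraph describes 36 items in six domains, each item coded 0 to 4. The abstract also calls the primary outcome a 36-item total score.

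Sample size {14} uses a different label: "We have based the sample size calculation on the sum of domain scores of the WHODAS 36". The figures come from 25 randomly selected clinic patients: "These patients had a mean sum of domain scores of 17 (SD=4"). The effect is set by "The minimally important clinical difference on the WHODAS 36 is about a 10% change in scores", and the stated result is 63 per group for "80% power to detect a 10% change in scores" at an alpha of 0.05.

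Two other rules use the same instrument. Inclusion criterion 4 in Table 1 reads "Have a minimum WHO Disability Assessment Scale (WHODAS) self-report (36 item) sum score of 15". The trial-level stopping rule under {11b} counts intervention-group participants with "at least a 20% increase in severity in their WHODAS sum score".

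No section gives a score range, says whether a domain score is a sum or an average of its items, or states whether the two labels mean the same score.

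**The concern.** A power statement is useful only if its mean, SD and target difference belong to the variable that will be analysed. Here the planning score has its own name and no defined scoring. Its values also sit oddly on the scale that the outcome section suggests. On 0 to 144, a mean of 17 is less than half a point per item, between none and mild, in patients attending a Long COVID clinic.

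Two things are at stake. The target is a percentage of the mean, so it depends on where the scale's zero lies and on the ratio of SD to mean. The entry minimum of 15 also means very different things on different scales: it may exclude almost nobody, or about a third of the population on which the trial was planned.

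**Working it through.** **Inputs.** Mean 17, SD 4, 10% difference, alpha 0.05, 80% power and 63 per group come from Sample size {14}. The 36 items, 0 to 4 coding and six domains come from the primary outcome section, and the minimum of 15 from Table 1. Alpha is taken as two-sided because the article does not say.

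**1. The plan's own figure.** The difference is 0.10 × 17 = 1.7, so d = 1.7/4 = 0.425.
- n per group = 2(1.96 + 0.8416)²/d² = 15.70/0.1806 = 86.9, so 87 (174 in total). The t-test version gives 88.
- Power at 63 per group = Φ(0.425 × √(63/2) − 1.96) = Φ(0.425) = 0.66 (t-test 0.66).
- One-sided, n is 69 per group and power at 63 is 77%.

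The stated 63 is not reproduced. It matches d = 0.5 (15.70/0.25 = 62.8), that is, a difference of 2.0, or 11.8% of 17. It would also follow from baseline adjustment with an unstated correlation of about 0.53.

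**2. Candidate scales for 17 (SD 4).**
- Item total: 36 × 4 = 144. Then 17/36 = 0.47 per item, and 17 ± 1.96 × 4 is about 9 to 25 out of 144.
- Sum of six domain averages coded 0 to 4: range 0 to 24, and 17/24 = 71% of the maximum.
- Sum of six domain averages coded 1 to 5 (assumption): range 6 to 30, and 17 − 6 = 11 on the 0 to 24 scale.

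**3. Effect of scale on sample size.** With the target fixed at 10% of the mean, n depends only on SD/mean:

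| SD/mean | n per group for 80% power |
|---|---|
| 0.20 | 63 |
| 4/17 = 0.235 | 87 |
| 0.30 | 142 |
| 0.40 | 252 |
| 0.50 | 393 |

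- Proportional case: multiplying by 6 gives mean 102 and SD 24. The difference is 10.2, d is still 0.425, and n is still 87.
- Offset case (pilot coded 1 to 5): mean 11, SD 4, difference 1.1, d = 0.275. Power at 63 per group is 33% by t-test (34% by normal approximation), and 80% needs 208 to 209 per group.

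**4. The entry minimum.**
- If 15 is on the planning score: z = (15 − 17)/4 = −0.5, so 31% fall below it (normal assumption). With λ = 0.3521/0.6915 = 0.509, the remaining mean is 17 + 4 × 0.509 = 19.0. The SD is 4 × √(1 − 0.5 × 0.509 − 0.509²) = 2.8. If that SD also held at 12 weeks, d = 1.9/2.8 = 0.68 and about 34 per group would suffice.
- If 15 is on 0 to 144 and the pilot used domain averages: 15/6 = 2.5 on 0 to 24 (equal weights). That excludes about 2% when the pilot mean is 11, and practically nobody when it is 17.

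**5. The 20% trigger.** It is relative, so a multiplier leaves it unchanged. An offset does not: 20% of 17 is 3.4 points, while 20% of 11, for the same average patient, is 2.2.

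**The case against.** A reader might infer that the planning score, the primary outcome, the entry minimum and the harm trigger are on different scales. The document does not prove that. If domain scores are item sums, their sum is the 36-item total. If the sum score means the sum of six domain averages throughout, every section again refers to one score, and a minimum of 15 just below a mean of 17 fits that reading. The 0 to 144 range is derived, not stated. Table 1 and the stopping rule share the primary outcome's sum-score wording; only the sample size section differs. All of this stands.

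It is also tempting to report 33% power as the cost of a mismatch. That needs 1 to 5 coding, whereas the only coding in the article is 0 to 4. Against the 66% that the stated inputs deliver, scale would account for a fall from 66% to 33% at most in that scenario, and for nothing under proportional rescaling. Restricting entry may even move nominal power upwards, although truncating baseline scores does not fix the SD at 12 weeks.

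Finally, detailed scoring rules may sit in the full protocol or analysis plan. That answers a complaint about missing detail. It does not answer stated inputs that fail to reproduce the stated sample size.

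**Conclusion.** The concern holds in a limited form. The score behind 17 (SD 4) is undefined and carries a different label from the primary outcome, so its mean and SD are not shown to apply to the analysed score. Either reading leaves work to do. On one shared score, about 31% of the planning population is ineligible (assuming normality, with parameters from 25 patients), so the pilot mean and SD do not describe those enrolled. On two scores, the planning SD does not belong to the analysed score.

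The effect of scale on power has no single value. It is nil under proportional rescaling, possibly favourable under truncation, and as severe as 33% power (209 per group for 80%) under the unstated 1 to 5 coding. The firm figure does not depend on scale: with a difference of 1.7, SD 4 and two-sided 0.05, 63 per group gives about 66% power, and 80% needs 87 to 88. The stated 80% therefore rests on something that the article does not state.

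**What to change.** Name one WHODAS score, with its item coding, the way domains are combined and its range, and use that name in the primary outcome and sample size sections. Re-score the 25 existing pilot records on it, keeping those that meet the entry criterion. Then restate the mean, the SD, the 10% difference in points, the sidedness, any baseline adjustment with its assumed correlation, and the resulting power or sample size.

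The entry minimum in Table 1 and the 20% trigger under {11b} must be reconciled with the named score. What those thresholds should be is for the investigators, and no new values are proposed here.

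The cost is small: 25 records already in hand and a wording amendment, with one participant enrolled when the article was written. There are two downsides. The restated power may differ from 80%. If 15 is on the planning score, only about 17 records would remain (0.69 × 25), so the new SD would be imprecise and should be shown with a range.

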## Methods: participants, interventions, and outcomes

### Study setting {9}

This single-site study will be conducted at the Ottawa Hospital Research Institute (OHRI). Recruitment will occur through two different streams to increase the diversity of participants. The first stream is a clinic that sees Ontario workers who were infected by SARS-CoV-2 at their worksite, who have made a claim to the Ontario Workplace Safety and Insurance Board (WSIB) and are assessed by the Ontario Workers Network (OWN) based at The Ottawa Hospital (TOH). The second stream are clinics within TOH which are seeing patients with Long COVID. These are clinics specifically for people with Long COVID, for example within the rehabilitation service, or specialist clinics that are seeing people with Long COVID such as respirology, infectious diseases, or psychiatry.

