## Assignment of interventions: allocation

### Sequence generation {16a}

Randomization will be done remotely by the Ottawa Methods Centre (OMC) through an electronic randomization system. Participants will be randomized at enrollment by a delegated study staff member. As participants are created in the ECDS, they are automatically randomized. The delegated study staff member will be informed of the allocation at the time of randomization.

Allocation will be a 1:1 ratio into the treatment arms. Participants will be stratified by sex and duration of symptoms. The reasons for stratification by sex are that the mortality rate in males is higher than in females and that outcomes may be affected by gendered occupations [63–66]. We will stratify by the duration of symptoms into two groups: (1) those who at enrolment have had symptoms since the onset of their index illness for 12 to 23 weeks, and (2) those who have had symptoms at enrolment for 24 weeks or longer, which is consistent with the classification of Long COVID in the NICE guidelines. We are stratifying for duration of illness as this is one of the main determinants of outcomes.

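### The single 80% power figure rests on patients of one clinic with no stated score floor, and is not established for the population the trial will enrol

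*Protocol article*

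**What the plan says.** The section Sample size {14} of the protocol article takes its inputs from a small local sample: "we have based our sample size calculation on WHODAS 36 scores from 25 randomly selected patients attending an existing clinic for Long COVID at TOH", namely the clinic that OWN runs. It reports "These patients had a mean sum of domain scores of 17 (SD=4"). The effect is relative: "The minimally important clinical difference on the WHODAS 36 is about a 10% change in scores". The result is 126 participants, "63 in each group) to have 80% power to detect a 10% change in scores assuming an alpha of 0.05", raised to 152 for dropout. Allocation is 1:1 (Sequence generation {16a}).

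Two other sections define who enters the trial. In Eligibility criteria {10}, Table 1, inclusion criterion 4 is "Have a minimum WHO Disability Assessment Scale (WHODAS) self-report (36 item) sum score of 15". Study setting {9} has the OWN workers' clinic as the first stream and adds another: "The second stream are clinics within TOH which are seeing patients with Long COVID". Recruitment {15} repeats the two streams.

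The sample size section mentions neither the floor nor the second stream.

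**The concern.** A mean and SD used for sizing should describe the people who will be randomised. Here they describe attenders of one of the two streams, chosen at random, with no stated restriction on score. The trial restricts entry on the same instrument that serves as its primary outcome. If the scales match, the floor lies half an SD below the pilot mean, so it would raise the mean and narrow the spread. Because the target is a percentage of the mean, both the difference in points and the SD would change.

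What is at stake is whether the 80% can be relied on when the result is read, above all if the trial is inconclusive. Recalculating at mean 17 and SD 4 alone would leave the figure tied to a population that is not the enrolled one.

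**Working it through.** **Inputs.** Mean 17, SD 4, a 10% change, alpha 0.05, 63 per group (Sample size {14}); floor 15 (Eligibility criteria {10}); 1:1 allocation (Sequence generation {16a}). Sidedness is not stated; two-sided is taken. The comparison is an unadjusted difference in two means.

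**1. The plan's own figure.**
- Difference = 0.10 × 17 = 1.7 points; d = 1.7/4 = 0.425.
- n per group = 2 × (1.960 + 0.842)² × 4² / 1.7² = 86.9, so 87 (88 by t-test), not 63.
- Power with 63 per group = Φ(0.425 × √(63/2) − 1.960) = Φ(0.425) = 66%.
- A one-sided test gives 69 per group (70 by t-test) and 77% power.
- 63 is obtained with a difference of 2.0 points, which is 10% of 20 rather than 17. It is also obtained with baseline adjustment at a correlation of 0.53. The section states neither.

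**2. Effect of the floor on baseline scores.** Assumptions: normal scores, and 15 and 17 on one scale.
- a = (15 − 17)/4 = −0.5; share below the floor = Φ(−0.5) = 30.9%, about 8 of 25.
- λ = φ(0.5)/0.691 = 0.509; eligible mean = 17 + 4 × 0.509 = 19.04.
- Eligible SD = 4 × √(1 − 0.5 × 0.509 − 0.509²) = 2.79.

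**3. Carry-over to week 12.** The arms are compared at week 12, so both the mean and the SD must be taken there. With baseline to week-12 correlation r (assumed; the document gives none) and no change over time other than regression to the mean:
- mean = 17 + r × 2.04
- SD = √(16(1 − r²) + r² × 2.79²)

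| r | Week-12 mean | Week-12 SD | 10% of mean | Power, 63 per group (normal / t) |
|---|---|---|---|---|
| 0.3 | 17.61 | 3.91 | 1.76 | 72% / 71% |
| 0.5 | 18.02 | 3.73 | 1.80 | 77% / 77% |
| 0.7 | 18.43 | 3.46 | 1.84 | 85% / 84% |

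**4. If the scales differ.** Outcomes {12} scores 36 items from 0 to 4, so an item sum runs from 0 to 144. Suppose the pilot figure is instead a sum of six domain averages. A floor of 15 out of 144 then converts to 15/144 × 24 = 2.5 on a 0-24 range, or 6 + 2.5 = 8.5 on a 6-30 range. The share below is Φ(−3.625) = 0.01% or Φ(−2.125) = 1.7%. The eligible mean is 17.00 or 17.17, and power with SD 4 stays at 66-67%.

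**5. Second stream.** No scores are given. Purely as illustration, a mean of 19 with SD 3, 4 or 5 gives about 94%, 76% or 57% power with 63 per group.

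**The case against.** The strongest reply is that the effect of the floor cannot be sized from the document. The pilot figures are a sum of domain scores, while the floor is a 36-item sum score, and nothing says the two are the same scale. Step 4 shows that on one plausible reading the floor removes almost nobody. This stands: the 31% and the table are conditional on a common scale.

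The pilot is also noisy. With 25 patients, the 95% interval for the SD is about 3.1 to 5.6 under normality, which moves power at 1.7 points from about 86% to 40%. The section also explains why local data were used: no published Long COVID scores existed. Both points are fair. They argue for stating a range, not for leaving one figure in place.

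Three stronger readings are tempting but unsupported:
- A reader might infer that the floor costs power. On a common scale it raises power above the 66% that the plan's inputs give.
- A reader might take 10% of the eligible baseline mean and divide by a week-12 SD, which gives higher power. That mixes time points, because the week-12 mean regresses towards 17 under the same selection model.
- A reader might infer that 17 is a control-arm mean, or that a point threshold for judging the result is set too low. The document calls 17 only the mean of the sampled patients, and it states a percentage with no point threshold.

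**Conclusion.** The mismatch is in the text and does not depend on the scale. The planning mean and SD come from one clinic with no stated floor; the trial imposes a floor and adds other clinics; nothing reconciles them. The stated 80% is therefore not established for the enrolled population, and the plan's own inputs give about 66%.

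The size of the floor's effect is conditional. With normal scores, one common scale and correlations from 0.3 to 0.7, power with 63 per group is about 71% to 85%. If 15 is a 0-144 item sum, it stays close to 66%. The second stream could move power either way, and the document gives no figure for it. Nothing here shows that the trial needs more participants because of the floor. That step 1 does not reproduce 63 per group is a separate error, and correcting it alone would not cure this one.

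**What to change.** In Sample size {14}:

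1. State one WHODAS scoring and use it for the entry floor, the sizing and the primary outcome.
2. If the floor and the pilot scores are on that same scale, recompute the planning mean and SD from the pilot patients who meet the floor, adding second-stream scores if any exist.
3. State the 10% difference in points on the week-12 scale.
4. Replace the single 80% with the power of the planned 126 analysed participants, given as a range over stated SDs and baseline to week-12 correlations, and state the sidedness.
5. Keep the recruitment target of 152.

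The cost is a short re-analysis of the pilot scores, presumably still held, and a wording change. The drawback is precision: on a common scale only about 17 of the 25 pilot patients would be expected to meet the floor, which is why a range is needed.

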### Plans to promote participant retention and complete follow-up {18b}

A major difficulty in all clinical research is ensuring participants attend their visits and stay enrolled in the study. Efforts will be made to minimize the time between being approached about the study and the baseline visit. We anticipate lost to follow-up to be no more than 20%. While there is currently no available literature on the lost to follow-up rates for Long COVID rehabilitation, the case management platform we are using has demonstrated significantly higher levels of retention in difficult to treat populations [24]. For those participants in the intervention arm, daily and weekly reminders will be programmed into the NexJ Connected Wellness platform to encourage regular use and increase connectedness with the platform, increasing retention.

We will implement an escalated approach if contact is lost with individuals between study visits. The appropriate response will be determined in collaboration with the Principal Investigator, particularly if there is a potential safety concern. If contact is made with the participant and they are no longer interested in participating, the delegated study staff member will make every effort to ascertain why they are withdrawing their consent. Participants will be sent the link to complete their self-report questionnaires at each time point unless they have withdrawn their consent for participation.

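### On the protocol's own mean and SD, 63 per group gives about 66% power for a 10% change, not 80%, and 152 recruits do not leave 126 completers after 20% loss

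*Protocol article*

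**What the plan says.** All of the inputs stand in one paragraph of the protocol article, Sample size {14}:

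- **Source of the mean and SD:** "we have based our sample size calculation on WHODAS 36 scores from 25 randomly selected patients" at an existing Long COVID clinic. Their mean sum of domain scores was 17, with an SD of 4.
- **Target difference:** "The minimally important clinical difference on the WHODAS 36 is about a 10% change in scores".
- **Result:** "we need to recruit at least 126 participants (63 in each group) to have 80% power to detect a 10% change in scores". Alpha is set at 0.05. The text presents this as following from the assumptions just listed.
- **Drop-out:** "Allowing for 20% drop out would mean a recruitment target of 152 (76 in each group) people".

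Elsewhere, Sequence generation {16a} fixes 1:1 allocation, and the retention section {18b} expects loss to follow-up of at most 20%. The sample size paragraph does not say whether alpha is one- or two-sided. It gives no baseline correlation, no SD of change and no variance reduction for repeated measures.

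**The concern.** The printed inputs determine the sample size for a comparison of two means, and they do not give 63 per group. They give a number more than a third larger. The step from 126 to 152 multiplies by 1.2 where it should divide by 0.8, so the target does not protect the number said to be needed.

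The sample size rests on the primary outcome, and {11b} rules out stopping for benefit, so the final comparison carries the conclusion. A reader who trusts the 80% will take a null result as fairly strong evidence against a 10% effect. On the stated inputs the risk of missing such an effect is about 34%, against the 20% implied.

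**Working it through.** **Inputs.** Mean 17, SD 4, 10% change, 80% power and alpha 0.05 (all from Sample size {14}); 1:1 allocation ({16a}); 20% loss ({14} and {18b}). Two-sided alpha is my reading; the plan to report 95% confidence intervals in {20a} supports it. One-sided is also tried.

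**Step 1: reproduce the stated 63.** The formula is n per group = 2(z₁₋α/₂ + z₁₋β)² / d², with 1.960 + 0.842 = 2.802.

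- With d = 0.5 (2.0 points over SD 4): 2 × 2.802² / 0.5² = 62.8, so 63 per group. This is the stated figure.
- But 2.0/17 = 11.8%, not 10%. Rounding 1.7 up to 2 would explain it, though that is inference.

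**Step 2: use the stated 10%.** The difference is 0.10 × 17 = 1.7 points, so d = 1.7/4 = 0.425.

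- 2 × 2.802² / 0.425² = 86.9, so 87 per group (174 in total). The t-test gives 87.9, so 88 per group (176 in total).

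**Step 3: power of the stated design for 1.7 points, two-sided 0.05.**

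| Evaluable per group | Normal approximation | t-test |
|---|---|---|
| 61 (about what 152 leaves after 20% loss) | 65.1% | 64.4% |
| 63 | 66.5% | 65.8% |
| 76 (all 152, no loss) | 74.5% | 74.0% |

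Even complete retention of all 152 does not reach 80%.

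**Step 4: detectable difference at 63 per group, 80% power.** Normal approximation: 4 × 2.802 × √(2/63) = 2.00 points, 11.7% of 17. t-test: d = 0.503, or 2.01 points, 11.8% of 17.

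**Step 5: one-sided 0.05.** The requirement is 69 per group (t-test 70), and 63 per group gives 77% power. This does not reproduce the figure either.

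**Step 6: drop-out.**

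- 126 × 1.2 = 151.2, rounded up to 152 (76 per group). This is how the stated target arises.
- 152 × 0.8 = 121.6 completers (60.8 per group), below 126.
- Correct inflation: 126/0.8 = 157.5, so 158 (79 per group).
- Loss that 152 can absorb while keeping 126: 1 − 126/152 = 17.1%.

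**Step 7: recruitment needed to meet the stated aim on the stated inputs.** 87/0.8 = 108.75, so 109 per group (218 in total). From the t-test, 88/0.8 = 110 per group (220 in total).

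**The case against.** The arithmetic on the printed inputs is not in dispute. Four points can be made about its weight.

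*Rounding.* The mean and SD are printed as whole numbers. A mean of 17.49 with SD 3.50 would print as 17 and 4, and gives d = 0.4997 and n = 62.9, hence 63. That is possible, but it needs both figures at the favourable edge at once. With mean 17 and SD 3.5 the need is still 67 per group. Across the full rounding range, n runs from about 63 to about 116 per group, and t-test power at 63 from about 53% to 79%. So 66% is the central value of a wide range, and no part of that range reaches 80% by t-test.

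*Baseline adjustment.* The WHODAS is measured four times, and {20a} plans a hierarchical regression. In a baseline-adjusted week-12 comparison, a baseline to week-12 correlation of about 0.52 would bring the need down to 63 per group (87 × (1 − 0.525²) = 63.0). At 0.6, power at 63 would be about 85%. This stands as a limit on the consequence: the eventual analysis may do better than 66%. It does not rescue the paragraph, which states no correlation and attributes 126 to assumptions that do not include one.

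*Drop-out.* The expected 20% is an upper bound, the analysis is intention-to-treat, and multiple imputation is planned above 5% missingness. The error is six recruits and one to two points of power. It is minor by itself, although imputation does not replace the lost information.

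*Misreading of a null result.* A 95% confidence interval would show whether 1.7 points is excluded, whatever the planned power. That is true, and it tempers the harm without making the stated power correct.

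**Conclusion.** The concern holds. The statement of 80% power for a 10% change does not follow from the assumptions given for it. For an unadjusted comparison of two means with mean 17, SD 4 and two-sided 0.05, 63 per group gives about 66% power for 1.7 points, or 80% for about 2.0 points (about 12%). The shortfall against the protocol's own aim is 174 − 126 = 48 evaluable participants. The target of 152 holds 126 completers only up to 17% loss, not the 20% it claims to allow for; this second error is small. The 66% depends on the rounded pilot figures and on no gain from baseline adjustment. Because the primary power statement is false on its own inputs, it must be corrected.

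**What to change.** Rewrite the sample size paragraph so that its figures agree:

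1. Say that 63 evaluable per group gives about 66% power for 1.7 points (10%), or 80% power for about 2.0 points (12%), at two-sided 0.05, and state the sidedness.
2. Either raise the target to 158 (79 per group) for 20% loss, or keep 152 and say that it allows for 17% loss.
3. If a baseline-adjusted week-12 analysis is made primary, restate power on that basis with the assumed baseline to week-12 correlation and its justification.

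The cost is one paragraph and a less favourable stated power, plus six recruits if 126 completers are to be kept at 20% loss. Note that 158 protects 126 completers; it does not restore 80% power for 10%. Without baseline adjustment, that aim needs 174 to 176 evaluable, or 218 to 220 recruited. The sponsor should choose openly between the larger trial, the larger detectable difference and an adjusted analysis with stated assumptions.
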